##### Cost-minimisation analysis

We will use a cost-minimisation analysis in this study, since this health care intervention has a similar medical outcome for both groups, i.e. surgical outpatient treatment [5]. The analysis will have a public health provider perspective. This includes travel costs, since the public health service pays for these costs in Norway. Direct health care costs that are the same in both alternatives will be excluded. The costs for the GPs providing this service will include investment, support, and time costs. Costs of traditional referral will include hospital administration, examination at the Surgical Outpatient Department (surgeon time, nurse time), surgical treatment at the Department of Day Case Surgery (surgeon time, anaesthetist time, and nurse time) unused surgical capacity due to incorrect referral, and patient travel costs. All costs will be estimated separately and compared between the two groups.

We will then conduct a threshold analysis. This analysis calculates the number of patients needed to break even, i.e. where the cost of providing a one-stop service equals the cost of traditional referrals.

This value is given by:

Total cost of one-stop service = Total cost of traditional referral

F_OS _+ xV_OS _= F_TR _+ xV_TR_

X = (F_OS _+ F_TR_)/(V_OS _- V_TR_)

X = number of consultations; F = fixed costs; V = variable costs; OS = one-stop; TR = traditional referral;

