#### Analysis

Treatment arms will be compared with respect to potential covariates using continuous and categorical variables. This will include variables related to patients (sex, age, type of disease, date of referral, date of outpatient examination, date of outpatient surgery), cost (patient sick leave, GP examination, hospital administration, surgical outpatient examination, surgical outpatient treatment, unused surgical capacity due to incorrect referral, patient travel cost). The results will be presented as intention-to-treat analyses and treatment analyses.

We will conduct analyses using the latest version of SPSS. The trial will be reported according to the CONSORT standards for reporting randomised trials [6,7].

The results will be expressed as an odds ratio (for binary outcomes), hazard ratio (time to event outcomes) or mean difference (for continuous outcomes) with corresponding standard errors, 95% confidence intervals and associated p-values. For all two-sided tests we use alpha = 0.05 level of significance.

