A general-practice-led model of integrated care can significantly reduce outpatient attendance while improving patient experience for patients with menorrhagia [17,18]. For patients with lower urinary tract symptoms and hematuria, a guideline-based open-access investigation service streamlined the process of outpatient referral and resulting in a decrease in waiting time and fewer outpatient investigations [19]. For patients with breast lumps, a one-stop clinic approach and referral guidelines have been shown to be feasible [20-22].

After the introduction of the Norwegian Health Care network, all referrals and discharge letters from hospitals in North Norway are sent electronically between primary and secondary care. Despite this improvement, poor communication often results in inefficiencies and unsatisfactory outcomes. Studies show that both referral and discharge letters were missing vital medical information, referral letters to such an extent that it might represent a health hazard to older patients [23]. Furthermore, poor communication results in unnecessary consultations, as well as delay in diagnosis and treatment [24-26].

This study is defined as a complex intervention, i.e. an intervention that includes several components (guidelines, electronic standardised referral and booking for outpatient surgery) [27]. This trial is directed at health professional behaviour with a strategy for implementing guidelines and computerised decision support. According to Campbell et al., it is useful to consider the process of development and evaluation of such interventions as having several distinct phases (theory, modelling, exploratory trial, definitive randomised controlled trial and long-term implementation). In this trial we will follow these phases, where this study protocol describes these phases and how we will conduct the definitive randomised trial.

An important decision in trials of complex interventions is whether health outcome needs to be assessed. In this "one-stop trial", all patients are receiving the same treatment (day case surgery) in both trial arms. In our opinion it is therefore sufficient to investigate the possible change of health care behaviour, decreased waiting time and increased cost benefit induced by the intervention.

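### The cost-minimisation plan contradicts itself on cost items, perspective and equal treatment, and read literally its item lists favour one-stop

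*Protocol article*

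**What the plan says.** The Abstract names waiting time and costs as the primary endpoints, and the cost-minimisation section stands under the primary outcome. That section contains these statements:

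- Perspective: "The analysis will have a public health provider perspective". Travel is included on the stated ground that the public health service pays for it.
- Exclusion rule: "Direct health care costs that are the same in both alternatives will be excluded".
- One-stop: "The costs for the GPs providing this service will include investment, support, and time costs".
- Traditional referral: "Costs of traditional referral will include hospital administration, examination at the Surgical Outpatient Department (surgeon time, nurse time), surgical treatment", followed by theatre staff time, surgical capacity wasted through incorrect referrals, and travel.
- Comparison: every cost is to be estimated separately and compared between the groups. Fixed and variable costs for each arm then enter a break-even equation.
- Premise: cost-minimisation is used "since this health care intervention has a similar medical outcome for both groups, i.e. surgical outpatient treatment".

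The Analysis section compares the arms on a list that begins "cost (patient sick leave, GP examination, hospital administration" and goes on to clinic examination, surgery, wasted capacity and travel, without naming an arm. The Objectives section frames cost-effectiveness as the hospital's. The Control arm section has the clinic surgeon decide whether an operation is indicated. The Discussion states that "all patients are receiving the same treatment (day case surgery) in both trial arms".

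**The concern.** The break-even equation needs a variable cost for each arm, V_OS and V_TR. The two sentences in the cost-minimisation section are the only arm-specific lists in the document. An analyst who follows them literally puts surgery and all travel into V_TR and neither into V_OS, although patients in both arms travel to surgery and have it. The difference between the arms is then too large and the break-even number too small.

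Capacity lost to incorrect referral is the item placed least convincingly. In one-stop the GP books the theatre slot and no surgeon examines the patient first. In the control arm a surgeon has already examined the patient. Such losses are at least as plausible in one-stop, yet the item is named under traditional referral.

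Two further conflicts affect what the cost result means. The boundary of the analysis is not the same in the three places that describe it. And cost-minimisation rests on equal treatment, which the plan's own description of the pathways does not guarantee.

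**Working it through.** The protocol gives no unit costs, no rate of incorrect referral and no break-even figure, so there is no figure to reproduce. The check is a comparison of the text, followed by an illustration on assumed costs.

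**1. Item lists.** If surgery costs the same in both arms, the exclusion rule removes it and it should not be listed. If it differs, it belongs in both arms' totals. Neither case matches a listing under one arm. The Analysis list also includes surgery, omits one-stop investment and support, and adds sick leave. No single list is complete for both arms.

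**2. Perspective.** There are three boundaries: public provider (cost-minimisation section), hospital (Objectives) and a list with patient sick leave (Analysis). Travel is justified under the provider perspective by who pays; no such reason is given for sick leave.

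**3. Equal treatment.** Per randomised patient, the surgery cost is p × S, where p is the share operated on and S the cost of surgery. The arms differ by (p_TR − p_OS) × S, which is zero only if the shares are equal. The control pathway lets the surgeon decline to operate, and the plan expects some referrals to be incorrect, so equal shares cannot be taken for granted. The sign of the difference is unknown.

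**4. Illustration; every input is assumed.** The unit is one clinic examination. Examination 1, trip 1 (two trips in traditional referral, one in one-stop), administration 0.5, GP time for one-stop 0.3, F_OS = 100, F_TR = 0. S runs from 0 to 10. A share w of one-stop slots is lost; no loss is assumed in traditional referral.

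- Literal lists: V_TR = 0.5 + 1 + 2 + S = 3.5 + S and V_OS = 0.3, so the difference is 3.2 + S.
- Common list: V_TR = 3.5 + S and V_OS = 0.3 + 0.5 + 1 + S + wS = 1.8 + S(1 + w), so the difference is 1.7 − wS.
- Break-even, solved from the protocol's equality of total costs: X = (F_OS − F_TR)/(V_TR − V_OS). The printed solution has different signs; that is a separate matter.

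| S | w | Literal difference | Literal X | Common difference | Common X |
|---|---|---|---|---|---|
| 0 | any | 3.2 | 31 | 1.7 | 59 |
| 2 | 0 | 5.2 | 19 | 1.7 | 59 |
| 5 | 0 | 8.2 | 12 | 1.7 | 59 |
| 5 | 20% | 8.2 | 12 | 0.7 | 143 |
| 10 | 0 | 13.2 | 8 | 1.7 | 59 |
| 10 | 20% | 13.2 | 8 | −0.3 | none |

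The row S = 0 shows that dropping surgery alone is not enough: administration and the trip to surgery remain one-sided. With a common list and no lost slots, the cost of surgery has no effect. Lost slots do matter, and the exclusion rule does not settle them, since they need not be equal in the two arms.

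**The case against.** A reader might infer that the plan charges surgery and wasted capacity only to traditional referral, and so favours one-stop by construction. The document does not fix that. The one-stop sentence describes GP costs and is not worded as a closed list for the arm. The section says that all costs will be compared between the groups. The Analysis list names no arm and contains surgery, lost capacity and travel. The Data gathering section says data are collected identically in both arms. If the exclusion rule and that list are applied to both arms, the one-sided loading disappears. This part of the objection stands, and limits the finding to inconsistent drafting with a biased literal reading.

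A reader might also put a multiple on the overstatement: 1 + k if surgery costs k times the avoided clinic visit. The protocol gives no value for k, and the multiple ignores the avoided trip. At k = 5 it gives 6, whereas the assumed inputs above give 8.2/1.7 = 4.8. No multiple can be claimed.

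The remaining objections stand in part. Sick leave is listed as a compared variable and is not said to enter the cost-minimisation total; the hospital wording may be loose. One-stop has guidelines and mandatory information, and unbooked slots are released two weeks ahead, so a higher rate of lost slots there is plausible but not shown. Eligibility is limited to conditions that the GP judges to need surgery, and the Discussion argues openly against measuring health outcomes. That is a disclosed choice. It does not remove the conflict with conditional surgery in the control arm. Demanding complication and readmission counts would go too far: with about 60 patients per arm, similar counts of rare events would not establish equality.

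**Conclusion.** The point holds as an internal inconsistency in a primary endpoint. The cost-minimisation section's arm-specific lists, its exclusion rule and the Analysis list cannot all be followed. Taken literally, the arm-specific lists inflate V_TR relative to V_OS, favour one-stop and lower the break-even number. The perspective and equal-treatment conflicts are also real, but neither has a fixed direction.

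Neither the size nor the net direction of the effect on the final result can be stated, because the protocol gives no unit costs and no incorrect-referral rate. The table rests wholly on assumed costs. It shows only that the choice of list can move the break-even number substantially, and that lost slots in one-stop can remove the saving. The waiting-time endpoint is not affected.

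**What to change.** Reconcile the Objectives, cost-minimisation and Analysis sections as follows.

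- **One list.** Apply the same items to every randomised patient in both arms: GP time, administration, clinic visit, surgery where its cost differs between arms, unused or cancelled slots, and travel. Add investment and support for one-stop. Derive V_OS and V_TR from this list.
- **One perspective.** Use the stated public provider perspective for the base case. Show sick leave only in a separate scenario, and align the hospital wording in the Objectives.
- **Equal-treatment premise.** From the weekly chart review, report by arm the patients not operated on and the slots lost to incorrect referral. If these differ, qualify the cost-minimisation conclusion.

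The cost is some rewording and a few extra items from charts that are already reviewed weekly. The one-stop saving may look smaller.

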##### Intervention

The one-stop strategy is a set of interventions directed at GPs referring patients to the University Hospital. The interventions include: Guidelines for referral, standardised electronic referrals, booking for outpatient surgery and a patient information form.

Guidelines for referral: Guidelines for inguinal hernia, sinus pilonoidalis and gallstone disease were developed (Figure 3). All surgeons performing the surgical procedures reviewed the giudelines, and after a three-month period consensus was reached. The guidelines consisted of signs and symptoms for the condition, indications and contraindications for surgery, necessary blood samples and radiological examinations prior to surgery (for gallstone disease). Photographs of the condition were included in the guidelines for sinus pilonoidalis and inguinal hernia. These guidelines were implemented in the GPs electronic health record.

Standardised referral forms: Standardised referral forms were developed by specialists in gastrointestinal surgery in cooperation with GPs (Figure 2). These referral forms consisted of three parts: information needed for anaesthesia (mandatory), information needed for surgeons (mandatory) and additional information provided by the GPs. These referral forms were implemented in the GPs' electronic health records (Profdoc Winmed).

Booking of time, date and hospital for surgery: The booking system is integrated in the electronic health record (Profdoc Winmed); booking is done at the same time as referral. Patients can choose the optimal time and hospital for surgery. The system is managed by the Day Case Surgical Department. Available times and locations for surgery during a 6-month period are presented. Surgical capacity that has not been booked within two weeks of the relevant date is withdrawn and offered to patients who are not participating in the trial.

Patient information form: A patient information form (printable, integrated in the electronic health record) was prepared by a specialist in gastrointestinal surgery. The form included information about the place and time for surgery, information about the surgical procedure, and advice for the patient following surgery. Information about possible complications of surgery was also provided.

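### Both lists of cost items name unused theatre capacity only when a wrong referral caused it, so one-stop slots released at two weeks and still empty on the day fall outside the named item

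*Protocol article*

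**What the plan says.** The Abstract makes waiting time and costs the primary endpoints. The Cost-minimisation analysis section sets the viewpoint: "The analysis will have a public health provider perspective". It leaves out direct health care costs that do not differ between the alternatives.

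On the new service it says: "The costs for the GPs providing this service will include investment, support, and time costs". A second list opens with "Costs of traditional referral will include hospital administration, examination at the Surgical Outpatient Department" and ends with "unused surgical capacity due to incorrect referral, and patient travel costs". All costs are then compared between the groups and carried into a break-even calculation. The cost variables in the Analysis section contain the item in the same restricted form: "unused surgical capacity due to incorrect referral, patient travel cost".

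The Intervention section describes how GPs book theatre time. "Available times and locations for surgery during a 6-month period are presented". On slots nobody takes, the rule is: "Surgical capacity that has not been booked within two weeks of the relevant date is withdrawn and offered to patients who are not participating". Nothing says how a released slot that remains empty is costed, or how often that is expected.

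**The concern.** The item is defined by its cause. It captures theatre time lost because a patient was wrongly referred. Holding theatre time for GP booking is part of one-stop itself and creates a different loss: a slot that no GP books, that is offered elsewhere at short notice, and that nobody fills. No referral, correct or incorrect, belongs to that slot.

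From a public provider's viewpoint an empty, staffed theatre slot is a real cost. It arises from one alternative only, so the exclusion of costs common to both does not remove it. Leaving it out can therefore err only in favour of one-stop, on a primary endpoint and in the break-even number that would inform a decision to adopt the service. Charging wrong-referral losses to both arms would not help, because these slots would still be uncounted.

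**Working it through.** The article states no cost, slot count, refill rate or break-even number, so there is no figure of its own to reproduce. What can be checked is the direction of the effect and what its size depends on.

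**1. Does the named item reach these slots?** The two mentions of unused capacity (Cost-minimisation analysis; Analysis) carry the same qualifier. The only costs tied expressly to the new service are the GPs' investment, support and time. Neither covers a reserved slot that was never booked.

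**2. Break-even algebra.** The balance equation in the Cost-minimisation analysis section is F_OS + x·V_OS = F_TR + x·V_TR. Collecting terms gives x·(V_TR − V_OS) = F_OS − F_TR, so

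X = (F_OS − F_TR)/(V_TR − V_OS).

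The printed solution, (F_OS + F_TR)/(V_OS − V_TR), does not follow from that equation. With F_OS = 100, F_TR = 0, V_OS = 1, V_TR = 2 (arbitrary units), the equation gives 100/1 = 100 and the printed form gives 100/(−1) = −100. The direction below is therefore read from the solved equation.

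**3. Direction.** Suppose F_OS > F_TR and V_OS < V_TR.
- Empty slots entered as a fixed cost K: X becomes (F_OS + K − F_TR)/(V_TR − V_OS), which is larger.
- Empty slots entered as a variable cost: V_OS rises, the denominator shrinks, and X is larger.

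Either way, omitting the cost makes the calculated X too small.

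**4. What the size depends on (illustration; every input is assumed).** Let u be the share of reserved slots unbooked at two weeks, r the share of those refilled, and c the cost of an empty slot as a multiple of the variable saving V_TR − V_OS. With one slot per one-stop patient, there are u/(1 − u) unbooked slots per booked slot, so the idle cost per patient, in units of the saving, is

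i = c·u·(1 − r)/(1 − u).

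Entered as a variable cost, X is multiplied by 1/(1 − i). Taking u from 10% to 30% and c from 0.5 to 2:

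- r = 100%: i = 0, factor 1.00.
- r = 90%: from i = 0.5 × 0.1 × 0.1/0.9 = 0.006 to i = 2 × 0.3 × 0.1/0.7 = 0.086; factor 1.01 to 1.09.
- r = 50%: i = 0.028 to 0.429; factor 1.03 to 1.75.
- r = 0%: i = 0.056 to 0.857; factor 1.06 to 7.0. The middle case u = 20%, c = 1 gives i = 0.25 and a factor of 1.33.

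The result runs from nothing to large, and it turns mainly on the refill rate, which the text does not plan to measure.

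**The case against.** The strongest reply is that this is silence, not a rule. The lists say what costs will include; they are not closed. The sentence with the restricted item is worded for traditional referral, and a journal article may leave detailed costing to a fuller document. That stands against one tempting reading, that the plan fixes the cost of empty reserved slots at zero. The article does not say so. It does not remove the point, though: an open list does not widen an item that is itself defined by cause, and the same definition appears in two sections.

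The second reply is that the two-week release exists to get slots refilled. Table 2 gives a mean of 119 days from internal referral to day surgery, so there is a queue to draw on. This also stands: substantial refilling is plausible, and a reader should not infer that one-stop's cost is certainly understated. Complete refilling still cannot be presumed. Notice is at most two weeks, and the Abstract describes a scattered population with considerable travel costs.

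Third, a reader might try to size the loss by assuming one reserved slot per week at each of the three sites, or 3 × 52 = 156 over an assumed year. The article does not support that number. The Sample size section found 33 such patients in three months, about 33 × 4 = 132 a year, fewer than 156. Against the 366 treated in 2007 (Patients section), 156 would be 156/366 = 43% of all these operations, held for 60 one-stop patients. No size should rest on it.

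Finally, some slots may go unbooked only because the trial is small. Charging them in full could overstate what a routine one-stop service would cost. That is fair and shapes the fix.

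**Conclusion.** The point holds in conditional form. As described in both sections, the unused-capacity item does not cover one-stop slots that are released at two weeks and stay empty. If any do and they are not counted, the cost of one-stop is understated. The break-even number is then understated as well, provided that it is solved from the balance equation and that one-stop has higher fixed and lower variable costs than traditional referral.

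The size is unknown. It is zero with full refilling. In the illustration the break-even number would rise by 1% to 9% at 90% refilling and by 3% to 75% at 50%, all on assumed inputs. The article does not show that the bias is material. It does leave a one-directional cost of the intervention outside the named items of a primary endpoint, and the described items would not reveal whether it matters.

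**What to change.** In the Cost-minimisation analysis and Analysis sections, replace the single unused-capacity item with two:

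- (a) theatre slots lost in either arm because the referral was incorrect;
- (b) slots reserved for one-stop, released at two weeks, and still empty on the day.

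Count (b) from the booking system and report the refill rate of released slots. Cost (b) at the same staff-time rate as (a). Enter it as a cost of running one-stop and state whether it is fixed or variable, since the two change X differently. Use X = (F_OS − F_TR)/(V_TR − V_OS) for the break-even. Report the cost difference and the break-even number with and without (b), because part of (b) may reflect the small trial volume and not the service itself.

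The cost is a wording change and a modest extra count from a system that the Day Case Surgical Department already manages. The downside is that one-stop may look somewhat less favourable. If nearly all released slots are refilled, the count supports the sponsor's conclusion.

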#### Objectives

We wish to test the efficacy of the one-stop strategy in decreasing waiting time and increasing the cost-effectiveness of selected day case surgical outpatient procedures. We hypothesise that patients exposed to the one-stop strategy (intervention) will have decreased waiting time and increase the cost-effectiveness for the hospital, compared to patients who use the regular patient pathway, i.e. examination at the surgical outpatient clinic prior to outpatient surgery.

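### The break-even formula for the threshold analysis does not follow from its own equation and gives a negative patient number in the case the trial expects

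*Protocol article*

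**What the plan says.** The Abstract names waiting time and costs as the primary endpoints. Under Outcome measures, Cost-minimisation analysis, costs are first estimated and compared between the groups, and a threshold analysis follows. Its purpose is stated as: "This analysis calculates the number of patients needed to break even". Total costs are set equal as "F_OS _+ xV_OS _= F_TR _+ xV_TR", and the next line gives the solution as "X = (F_OS _+ F_TR_)/(V_OS _- V_TR". Both quotes lose a closing subscript mark, and the second also a bracket; the underscores come from text conversion.

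The key below the formula reads: "X = number of consultations; F = fixed costs; V = variable costs; OS = one-stop; TR = traditional referral".

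Two other statements bear on the signs:
- On one-stop costs, the same section says: "The costs for the GPs providing this service will include investment, support, and time costs". The one-stop fixed cost is therefore not zero.
- The Objectives section hypothesises that one-stop patients "will have decreased waiting time and increase the cost-effectiveness for the hospital". In a break-even setting this implies a lower variable cost per patient for one-stop.

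No other part of the article restates or corrects the formula.

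**The concern.** The solution line is inconsistent with the equation it is meant to solve. It adds the two fixed costs where their difference is needed. With F_OS written first in the numerator, the denominator is also the wrong way round.

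The threshold analysis turns the cost data into a volume: how many patients are needed before the set-up cost of one-stop is recovered. Followed as printed, it would report an impossible number in the expected case and a misleading one in others.

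There is also a labelling problem. X is the number of patients in the text and the number of consultations in the key. Under Control arm, a control patient has an outpatient examination and then surgery. Under Intervention, a one-stop patient is booked directly for surgery. If consultations means hospital contacts, the count per patient differs between arms and one common x cannot serve both sides of the equation.

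**Working it through.** **Inputs.** The equality, the printed solution and the key come from Cost-minimisation analysis. The article gives no cost amounts, so every cost below is an assumption used only to show how the formula behaves.

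**Algebra.**
1. Start: F_OS + x·V_OS = F_TR + x·V_TR.
2. Collect terms: x(V_OS − V_TR) = F_TR − F_OS.
3. Solve: x = (F_TR − F_OS)/(V_OS − V_TR) = (F_OS − F_TR)/(V_TR − V_OS).

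The printed form is (F_OS + F_TR)/(V_OS − V_TR). The denominators in step 3 (first form) and in the printed form agree, so the two coincide only if F_OS + F_TR = F_TR − F_OS, that is, only if F_OS = 0.

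**Sign.** With non-negative fixed costs that are not both zero, the printed numerator is positive. Whenever V_OS < V_TR the denominator is negative, so the printed X is always negative.

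**Size.** For F_OS > 0 and F_TR different from F_OS, put r = F_TR/F_OS. The ratio of printed to true value is (F_OS + F_TR)/(F_TR − F_OS) = −(1 + r)/(1 − r):
- r = 0: −1 (only the sign is wrong)
- r = 0.2: −1.2/0.8 = −1.5
- r = 0.8: −1.8/0.2 = −9

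**Numerical illustrations (assumed costs).**

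| F_OS | F_TR | V_OS | V_TR | Correct X | Printed X |
|---|---|---|---|---|---|
| 100000 | 20000 | 1000 | 2500 | 80000/1500 = 53.3 | 120000/(−1500) = −80 |
| 100000 | 0 | 1000 | 2500 | 100000/1500 = 66.7 | 100000/(−1500) = −66.7 |
| 100000 | 80000 | 1000 | 2000 | 20000/1000 = 20 | 180000/(−1000) = −180 |
| 20000 | 100000 | 2000 | 1000 | (−80000)/(−1000) = 80 | 120000/1000 = 120 |
| 100000 | 20000 | 2000 | 1000 | 80000/(−1000) = −80: no break-even | 120000/1000 = 120 |

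**Substituting back.**
- Row 1 at x = 53.3: one-stop 100000 + 53.3 × 1000 ≈ 153333; traditional 20000 + 53.3 × 2500 ≈ 153333. They balance.
- Row 4 at the printed 120: one-stop 20000 + 120 × 2000 = 260000; traditional 100000 + 120 × 1000 = 220000. They do not balance. At 80 both equal 180000.
- Row 5 at the printed 120: one-stop 100000 + 120 × 2000 = 340000; traditional 20000 + 120 × 1000 = 140000. One-stop is dearer at every volume, yet the formula returns a credible positive number.

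**Partial repairs, with F_OS 100000, F_TR 20000, V_OS 1000, V_TR 2000 (correct X = 80).** Changing only the plus to a minus, (F_OS − F_TR)/(V_OS − V_TR), gives −80. Reversing only the denominator gives 120. Neither is right.

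**The case against.** The strongest reply is about consequence. The equality is correct and stands just above the faulty line, so an analyst can solve it again, and a negative number of patients would be noticed. No test or success criterion depends on X, and the between-group cost comparison comes first and does not use it. All of this is true and limits the harm. It does not make the printed rule right, and when one-stop is dearer per patient the wrong answer is positive and raises no alarm.

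It can also be said that one sign is at fault, not two: the printed denominator is valid with the numerator F_TR − F_OS, so a minus lost before F_OS in typesetting or conversion would explain the line. The algebra is right, and that repair is identical to the one proposed here. That a sign was lost is conjecture, since the other operators in both lines survived.

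Two qualifications stand. The size is wrong only when both fixed costs are non-zero. If traditional referral has almost no fixed cost, which is possible because most of its listed items look variable, the error is in the sign alone; the contrast of 53 with −80 depends on the assumed F_TR of 20000. Second, consultations could mean the GP visit at which the patient is referred, one per patient in either arm. The mismatch of terms is then only one of labelling, though the article does not say which is meant.

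**Conclusion.** The formula is wrong as written. It contradicts the equation it claims to solve and is correct only if F_OS = 0, which conflicts with the planned investment and support costs. When V_OS < V_TR, the case implied by the trial's cost hypothesis, it returns a negative number whatever the amounts. For F_OS > 0 and unequal fixed costs, its value is −(1 + r)/(1 − r) times the true one, with r = F_TR/F_OS. The sign result for the expected case rests only on non-negative fixed costs with F_OS > 0. The illustrative patient numbers rest on assumed costs.

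The fault belongs to the cost analysis, one of the two primary endpoints, but is confined to its threshold step. The double naming of X is secondary and should be settled in the same correction.

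**What to change.** Replace the solution line with X = (F_OS − F_TR)/(V_TR − V_OS).

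State how it is read. A positive break-even exists when numerator and denominator have the same sign. If F_OS > F_TR and V_TR > V_OS, one-stop is cheaper above X; if both inequalities are reversed, one-stop is cheaper below X. If the signs differ, one pathway is cheaper at every positive volume and no break-even should be reported.

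Define X throughout as the number of patients referred, and V as the variable cost per referred patient over the whole pathway, including the outpatient examination in the control arm.

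The cost is one corrected line and one clarified definition. No change to data collection, sample size or the other analyses is needed.
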